#### Causal effect of community C(E)TRs on risk of hospitalisation

A two-stage framework will be applied to evaluate the causal effect of having a community C(E)TR on hospital inpatient prevalence after the C(E)TR; propensity score weighting (propensity model) and a difference-in-differences (DiD) analysis (outcome model). We will compare changes from the 6 months before the index date and the 6 months after the index date, between people with intellectual disability and autistic people who had a C(E)TR and those who did not. The outcome will be whether a person has a psychiatric inpatient admission at any time in the 6 months after the index date.

##### Stage 1: propensity scores

As the retrospective analysis of EHRs is not a randomised controlled study, we will employ a propensity score weighting technique to adjust for confounders in the data. Propensity scores will balance the C(E)TR and comparison groups on a set of baseline (pre-index date) characteristics.^12^ Certain characteristics may increase the probability of someone receiving a C(E)TR, and we wish to account for these in the outcome (risk of hospitalisation) model. Scores will be calculated by fitting a multivariable logistic regression model with C(E)TR status as the dependent variable.^13^ We will condition on baseline characteristics that are believed to be related to the outcome, risk of hospitalisation, and to the probability of receiving a C(E)TR (confounders), but not those that might lie on the causal pathway from receiving a C(E)TR to being admitted to hospital (mediators), that is, variables that are affected by the intervention itself. The following variables are expected to be included in the propensity score analysis: age, sex, ethnicity, marital status, sexual orientation, deprivation score, relevant diagnosis (intellectual disability with/without autism, or autism without intellectual disability) and pre-existing psychiatric diagnoses (online supplemental table 1).

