## Introduction

 Reducing unnecessary psychiatric hospital admissions and length of hospital stay for people with intellectual disability and autistic people has been a focus of English national health policy since the scandal of abuse and neglect of patients at Winterbourne View Hospital in 2011.^1^ The Transforming Care programme was established to improve community health and social care for people with intellectual disability and autistic people and to reduce what had generally been considered to be an over-reliance on inpatient psychiatric services.^2^ A key element of Transforming Care has been the introduction of Care (Education) and Treatment Reviews (C(E)TRs), person-centred review meetings that aim to ensure the right support is provided.^3^ A community C(E)TR should be convened when a person with intellectual disability or an autistic person living in the community is considered at high risk of admission to a psychiatric hospital, either because of mental ill-health or because of an escalation in behaviours that challenge. C(E)TRs are chaired by a health commissioner and include an independent clinical expert and an expert-by-experience, often a family carer of a person with intellectual disability or an autistic person. This panel gathers information from the individual, their families and carers, and professionals, and produces a report and action plan following the C(E)TR with recommendations (eg, input from specialist professionals or health teams, provision of additional care, use of respite services) that can enable the person to remain living safely in the community. Where admission to hospital is considered necessary, the C(E)TR panel will define the purpose of the admission and encourage early discharge planning in order to minimise the length of the hospital stay. Inpatient C(E)TRs are convened at various points of a hospital admission; the current project investigates only C(E)TRs that are held in the community.

Little formal research has been carried out on community C(E)TRs, such as who receives them and when, and how C(E)TRs may influence health service use, including admission to hospital. By understanding the demographic and clinical profile of patients who do, and do not, have a community C(E)TR, it may be possible to develop targeted interventions to improve access to community C(E)TRs and ensure the potential benefits are available to everyone.

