### Outcome

The primary outcome will be psychiatric hospital admission (treated as a binary variable) at any time within 6 months after the index date (online supplemental table 2).

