### Matching a control group

We will match between one and five controls, who will not have a community C(E)TR, per patient who has a C(E)TR. Eligibility will be a diagnosis of intellectual disability or autism and having received a continuous period of community care within SLaM services for at least a year between 1 January 2015 and 31 December 2023. Matching will be based on age (±3 years), sex (male/female) and diagnosis (intellectual disability with/without autism, or autism without intellectual disability). Controls should be under an active episode of community care and not be an inpatient on the index date of their matched case. They must also have been under SLaM services for a similar total duration of their matched case (±2 years). Matching with replacement will be applied to ensure every case has an appropriate match according to these criteria. A pseudo-index date for each control will be assigned and will be the same as the index date of their matched case.

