##### Stage 2: difference-in-differences (DiD) analysis

The DiD method compares changes in the prevalence of people admitted to hospital over time, contrasting the group who have a C(E)TR and the group who do not have a C(E)TR and attributes the ‘difference-in-differences’ to the effect of the intervention.^14 15^ Here, we will apply the DiD model to examine the causal effect of a C(E)TR on the prevalence of psychiatric hospital inpatient status at any point over the 6 months following the C(E)TR. Propensity scores will be included as weightings in the DiD analysis, following the method proposed in Stuart (2014). The estimand will be the average effect of the treatment on the treated. This is the average effect of receiving a C(E)TR on inpatient status, in the 6 months after the C(E)TR. The data to be entered into the DiD model is considered panel data—repeated-measures data from the same patients before and after the index date—thereby strengthening the causal claim. If the DiD model described above fails to converge or if important assumptions are not met (see Online supplemental appendixAppendix), we will use the propensity scores in a logistic regression analysis, with 6-month post-index date hospital inpatient status (yes/no) as the dependent variable and group (C(E)TR intervention/control) as an independent variable.

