#### Time-to-event analysis

Time-to-discharge (length of hospital admission) will be analysed using the Kaplan-Meier estimator.^19^ A Cox’s proportional hazards model will be used to estimate the HR for discharge,^20^ comparing those who received a C(E)TR to those who did not receive a C(E)TR for a follow-up period of 6 months after admission. This analysis will be adjusted for C(E)TR status prior to admission, age at admission, sex, ethnicity and relevant diagnosis at admission (intellectual disability with/without autism, or autism alone). Patients who die within 6 months of admission will be censored at the date of death, and patients who remain in hospital will be censored at the end of the 6 months.

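### The propensity set for sub-study 1 and, with less force, the Cox set for sub-study 2 omit the recent clinical risk that triggers a community C(E)TR, leaving the causal estimate open to substantial confounding by indication

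*Protocol article*

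**What the plan says.** The Introduction of the protocol article gives the trigger for a community C(E)TR. It is meant for a person "considered at high risk of admission to a psychiatric hospital, either because of mental ill-health or because of an escalation in behaviours that challenge". The primary outcome of sub-study 1 is "psychiatric hospital admission (treated as a binary variable) at any time within 6 months after the index date".

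Under Stage 1: propensity scores, the governing rule covers predictors of both admission and having a C(E)TR, and begins "We will condition on baseline characteristics that are believed to be related to the outcome, risk of hospitalisation, and to the probability of receiving"; mediators are left out. The list that comes after the rule opens with socio-demographic items: "The following variables are expected to be included in the propensity score analysis: age, sex, ethnicity, marital status, sexual orientation, deprivation score". To these it adds two diagnostic items, namely "relevant diagnosis (intellectual disability with/without autism, or autism without intellectual disability) and pre-existing psychiatric diagnoses". Under Matching a control group, "Matching will be based on age (±3 years), sex (male/female) and diagnosis", together with active community care at the index date and a similar total time under services.

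Table 1 and Descriptive statistics show that neuropsychiatric symptoms, clinical variables and service use are obtained for the 6 months before the index date. Their stated use is description and group comparison.

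The outcome model is a propensity-weighted DiD, 6 months before against 6 months after, with the average effect on the treated as estimand. If it does not converge or its assumptions fail, "we will use the propensity scores in a logistic regression analysis, with 6-month post-index date hospital inpatient status (yes/no) as the dependent variable"; the explanatory term is the C(E)TR or control group. No pre-index admission term is mentioned.

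In sub-study 2 the Cox model for time to discharge is specified as follows: "This analysis will be adjusted for C(E)TR status prior to admission, age at admission, sex, ethnicity and relevant diagnosis at admission". Pre-admission clinical and service-use variables are again only reported and compared. The HoNOS regression adjusts for baseline HoNOS, age, sex and ethnicity.

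**The concern.** Exposure is triggered by a clinical judgement that the outcome is close. The strongest predictor of receiving a C(E)TR is therefore also likely to be a strong predictor of admission, and it is recent by nature. None of the listed matching or propensity variables measures it. Two people of the same age, sex, ethnicity, deprivation and diagnoses can have the same propensity score while one is in crisis and the other is stable.

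The omission also sits badly with the protocol's own rule. Symptoms and service use recorded before the index date precede the C(E)TR, so the exclusion of mediators does not in general keep them out, and the confounder criterion points to including them.

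At stake is the causal reading of sub-study 1. A neutral or helpful review could appear to raise admissions. The 12-month analysis and the replication in the second Trust re-run the same models, so agreement between sites would not rule this out.

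**Working it through.** The article states no sample size, event rate or effect size, so there is no figure to reproduce. The check bounds the bias from one unadjusted binary confounder, recent escalation. **Every input below is an assumption.**

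**Inputs**
- p1, p0: share escalated at index in the C(E)TR group and in the weighted controls.
- R: ratio of 6-month admission risk, escalated to not escalated.
- r = 0.03: admission risk if not escalated.
- q1: share of the C(E)TR group escalated in the pre-index window; the control share is taken as constant.

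**Post-index comparison (the fallback model's contrast), no true effect**

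Apparent RR = [1 + p1(R − 1)] / [1 + p0(R − 1)]

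| p1 | p0 | R | Calculation | Apparent RR | If the true RR is 0.70 |
|---|---|---|---|---|---|
| 0.3 | 0.2 | 2 | 1.3 / 1.2 | 1.08 | 0.76 |
| 0.5 | 0.1 | 3 | 2.0 / 1.2 | 1.67 | 1.17 |
| 0.8 | 0.1 | 5 | 4.2 / 1.4 | 3.00 | 2.10 |
| 0.9 | 0.05 | 8 | 7.3 / 1.35 | 5.41 | 3.79 |

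In the third row the risks are 0.03 × 4.2 = 12.6% and 0.03 × 1.4 = 4.2%, a spurious +8.4 points. In three of the four rows a true benefit appears as harm.

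**DiD (the primary model), no true effect**

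Bias = r(R − 1)(p1 − q1). With p1 = 0.8, p0 = 0.1 and R = 5, this is 0.12 × (0.8 − q1).

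| q1 | Bias (percentage points) |
|---|---|
| 0.8 (escalation as common before index as at index) | 0 |
| 0.5 | +3.6 |
| 0.3 | +6.0 |
| 0.1 (escalation new at index) | +8.4 |

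For scale: with an untreated risk of 12.6%, a true RR of 0.70 is an effect of −0.3 × 12.6 = −3.78 points. The q1 = 0.5 bias leaves −3.78 + 3.6 = −0.18, close to nothing. The q1 = 0.3 bias gives −3.78 + 6.0 = +2.22, a reversal.

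So what matters for DiD is when escalation begins relative to the 6-month pre-window, and the document does not say. The formula would change sign if escalation were commoner in the pre-window than at index (q1 > p1). Upward bias is therefore likely, given the stated trigger, but not certain.

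**Sub-study 2.** No calculation was made. Set side by side, the Cox list contains no psychiatric diagnosis, deprivation, admission history or severity measure. The HoNOS model contains a severity measure but not the intellectual disability/autism category that the Cox model includes.

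**The case against.** A reader might infer that both sub-studies mainly estimate confounding by indication, or that parallel trends must fail. The documents do not support either. The DiD bias above is zero if escalation was as common in the pre-window as at index, and no figure in the article locates the truth within the range. The large post-index risk ratios belong to the fallback, not to the primary DiD.

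The protocol also has partial protection:
- The propensity list is only what is expected, and it includes pre-existing psychiatric diagnoses. The online supplemental tables and the appendix on DiD assumptions are not shown, so the exact variables cannot be checked, and the fallback's covariates may be condensed.
- Under Sensitivity analyses, the C(E)TR group may be compared directly with patients for whom a review was proposed but not shown to have happened. They probably share the indication. This is the right kind of comparison, but it is exploratory and optional, and in the main analysis these patients are in the control pool.

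For sub-study 2, a reader might infer that C(E)TRs will appear to lengthen stays. That is not shown. The sub-study is worded as comparison and association. Everyone was admitted for at least 14 days, so the risk of admission was realised in both groups. Admissions within 6 months of a previous discharge are excluded, and the HoNOS model already adjusts for baseline HoNOS. Naming C(E)TR status among the Cox adjustment terms is loose drafting without consequence.

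What stands is the omission itself. The stated direction is to use demographics and diagnoses for adjustment and recent clinical data for description, in an analysis that claims a causal effect.

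**Conclusion.** The concern holds for the causal analysis of sub-study 1 and, with less force, for the Cox model of sub-study 2. Recent clinical risk is the stated trigger, is at least partly measured before the index date, and is not in the listed adjustment sets. DiD handles stable differences only, so parallel trends is doubtful and the effect on the treated is open to substantial confounding by indication, probably towards apparent harm.

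The size is undetermined: 0 to +8.4 points for DiD in the scenario shown, and a null RR of 1.08 to 5.41 for a post-index comparison, all resting on assumed prevalences and risks. The fallback is the more exposed model. It would be used when DiD assumptions fail, which rising risk can cause, and it then states no pre-index outcome. The omission is certain as far as the article shows; the consequence is likely but not quantified.

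**What to change.** **Sub-study 1, propensity model.** Add, from before the index date: symptoms and behaviour (for example NLP-derived aggression), crisis or A&E use and other service use, medication, and psychiatric admissions earlier than the 6-month pre-window (admissions within it are already the DiD pre-period outcome). Leave out contacts that reflect preparation for the C(E)TR itself, since the article says these reviews need substantial planning. Report balance and overlap on the added variables.

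**Sub-study 1, fallback.** Include pre-index 6-month admission and the same variables as covariates in the logistic model.

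**Sub-study 2.** Add psychiatric diagnoses, deprivation and earlier admission history to the Cox model, and the intellectual disability/autism category to the HoNOS model. Use admission HoNOS in the Cox model only as a sensitivity analysis: it may be recorded up to 3 months after admission, so it can post-date the exposure and lie on its pathway.

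**Cost.** Protocol wording and modest analysis time. The symptom, clinical, service-use and inpatient-spell data are already to be extracted, and medication is listed as available in CRIS. The real downside is statistical: less overlap and larger weights. The number of C(E)TRs is unknown, so if few are found the covariate set must be kept small, with the priority variables chosen before outcomes are examined.

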### Study eligibility criteria

Individuals of any age with a diagnosis of intellectual disability (ICD-10 code F7x) or autism (ICD-10 code F84) will be identified using diagnostic information entered into structured fields or in the free text record using the NLP diagnosis application. Participants must have a recorded diagnosis of intellectual disability and/or autism. Eligible participants must have received an episode of care from a community mental health service provided by SLaM for at least one continuous year between 1 January 2015 and 31 December 2023 to ensure that sufficient data are held in the record. All eligible episodes of care will be included, including those individuals with more than one period of community care of at least 1 year during this timeframe.

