#### Sub-study 1: community cohort

Population, Intervention, Comparison and Outcome (PICO) framework (table 1).

**Table 1 T1:** Population, Intervention, Comparison and Outcome framework for sub-studies 1 and 2

	Sub-study 1	Sub-study 2
Population	People of any age with a recorded diagnosis of intellectual disability (ICD-10 code F7x), autism (ICD-10 code F84) or both, with at least 1 year of care under secondary mental healthcare services	People of any age with a recorded diagnosis of intellectual disability (ICD-10 code F7x), autism (ICD-10 code F84) or both, with at least 1 year of care under secondary mental healthcare services and an admission to a psychiatric inpatient ward for a period of at least 14 days
Intervention	Community C(E)TR	Community C(E)TR within 6 months prior to admission
Comparison	No community C(E)TR	Did not receive a community C(E)TR within 6 months prior to admission
Outcome		
Primary	Psychiatric hospital inpatient admission within 6 months of the community C(E)TR	Length of psychiatric hospital admission (days)
Secondary	Descriptive data and comparison of baseline demographics between intervention and comparison groups	Descriptive data and comparison of baseline demographics between intervention and comparison groups
	Descriptive data of 6 months pre-C(E)TR/post-C(E)TR (index date): neuropsychiatric symptoms, clinical variables and service use	Descriptive data and comparison of prehospital admission neuropsychiatric symptoms, HoNOS and service use Clinical and social functional improvement (change in HoNOS) while in hospital

C(E)TR, Care (Education) and Treatment Review; HoNOS, Health of the Nation Outcome Scales.

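### The diagnosis variable merges intellectual disability with and without autism in matching, the propensity score and the Cox model, which risks residual confounding that data already collected could reduce

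*Protocol article*

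**What the plan says.** Three steps of the protocol article define diagnosis in the same two-level way.

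- Matching a control group (sub-study 1): "diagnosis (intellectual disability with/without autism, or autism without intellectual disability".
- Stage 1, propensity scores: "relevant diagnosis (intellectual disability with/without autism, or autism without intellectual disability) and pre-existing psychiatric diagnoses". The list is introduced as provisional: "The following variables are expected to be included in the propensity score analysis". It points to online supplemental table 1, which is not shown.
- Time-to-event analysis (sub-study 2): "relevant diagnosis at admission (intellectual disability with/without autism, or autism alone". Apart from C(E)TR status itself, the other covariates are age at admission, sex and ethnicity.

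The two conditions are nevertheless ascertained separately. Under Study eligibility criteria, a "diagnosis of intellectual disability (ICD-10 code F7x) or autism (ICD-10 code F84) will be identified using diagnostic information entered into structured fields", or in free text by a natural language processing (NLP) application. Table 1 describes the population as people with "intellectual disability (ICD-10 code F7x), autism (ICD-10 code F84) or both, with at least 1 year of care".

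**The concern.** Stage 1 commits to conditioning on baseline characteristics thought to relate both to admission and to the chance of receiving a C(E)TR. By matching on diagnosis and adjusting for it, the plan already treats it as such a characteristic. It then places people with intellectual disability alone and people with intellectual disability plus autism in one category and gives no reason for doing so.

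The Introduction says a community C(E)TR is convened when admission risk is high because of mental ill-health or escalating behaviours that challenge. Co-occurring autism could plausibly bear on that risk, on being put forward for a review, and on time to discharge. If so, the share of people with both conditions may differ between the C(E)TR and comparison groups inside the merged category, and part of that difference would be read as an effect of the review. The direction cannot be foreseen: it depends on which group has more people with both conditions and on how that feature affects admission or discharge.

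**Working it through.** **Inputs from the document.** The diagnosis variable has two levels in all three steps. Autism and intellectual disability are identified separately, so three levels (intellectual disability only, both, autism only) can be built. The article gives no sample size, event count, effect size or association with co-occurring autism, so there is no stated figure to reproduce. All numbers below are assumptions chosen to show scale.

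**1. Exposure of each analysis.**

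| Analysis | Protection beyond two-level diagnosis | Exposure |
|---|---|---|
| Cox model, sub-study 2 | Age, sex, ethnicity; no matching, no weighting, no psychiatric diagnosis | Direct |
| Logistic fallback, sub-study 1 | Matching and propensity scores; post-index status only | Direct, for whatever the scores leave unbalanced |
| DiD, sub-study 1 | Matching, weighting and before-after differencing | Only if the feature's effect on risk changes over time |

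**2. Single-period risk ratio within the intellectual disability category.** Let *p1* and *p0* be the shares with the feature in the C(E)TR and comparison groups, and *RR* its risk ratio for the outcome. The bias factor is

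B = [1 + p1(RR − 1)] / [1 + p0(RR − 1)].

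With p0 = 0.30 (assumed):

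| RR | p1 = 0.30 | p1 = 0.40 | p1 = 0.60 |
|---|---|---|---|
| 1.2 | 1.00 | 1.08/1.06 = 1.02 | 1.12/1.06 = 1.06 |
| 1.5 | 1.00 | 1.20/1.15 = 1.04 | 1.30/1.15 = 1.13 |
| 2 | 1.00 | 1.40/1.30 = 1.08 | 1.60/1.30 = 1.23 |
| 3 | 1.00 | 1.80/1.60 = 1.13 | 2.20/1.60 = 1.38 |

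If the feature is balanced there is no bias. The formula describes a comparison of post-index risk, such as the fallback, and carries over only roughly to the Cox hazard ratio. It also assumes that the feature is unrelated to the covariates already adjusted for.

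**3. The same on the risk-difference scale.** Bias = (p1 − p0) × (risk with the feature − risk without it).

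- Shares 50% and 30%, risks 30% and 20%: 0.20 × 0.10 = 0.02, or 2 percentage points.
- Shares 60% and 25%, risks 30% and 10%: 0.35 × 0.20 = 0.07, or 7 percentage points.

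These hold inside the intellectual disability category. If that category were half the cohort (assumed), the whole-cohort figures would be 0.5 × 2 = 1 point and 0.5 × 7 = 3.5 points.

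**4. DiD on an additive scale.** Bias = (p1 − p0) × d, where d is the change in the feature's effect on admission risk from before to after the index date.

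- d = 0: bias 0, whatever the imbalance.
- d = 0.02, imbalance 0.10: 0.002, or 0.2 points.
- d = 0.10, imbalance 0.30: 0.03, or 3.0 points.

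**The case against.** The strongest reply is that two groups are a defensible modelling choice. The same split serves for matching, for description in sub-study 1 and for modelling. The article admits that the number of C(E)TR events is unknown and may be small, which favours coarse categories. Sub-study 2 is framed as a comparison, and only sub-study 1 sets out to model a causal effect. The propensity list is provisional, and its supplemental table and the content of the psychiatric diagnoses are not shown, so further detail may exist there. Finally, DiD removes the constant additive effect of a stable trait.

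Much of this stands, and it keeps the point small. It does not remove it. The parenthesis in each step still defines the diagnosis variable as two-level. The Cox covariate list is worded firmly and is not covered by the provisional wording in Stage 1. One extra parameter is a modest demand even with few events.

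A reader might infer more than the document supports:

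- **That level of disability is recorded and ignored.** The article gives only the code family, "intellectual disability (ICD-10 code F7x", and some diagnoses come from NLP, whose output in this study is binary. Level may be derivable for some people; its completeness is unknown.
- **That confounding has been shown.** No imbalance or association is reported.
- **That every adjustment step merges the groups.** The regression of change in HoNOS names no diagnosis term at all.
- **That people in the same diagnosis group receive equal weights.** The propensity score also uses other covariates.

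**Conclusion.** The point holds as a minor refinement. Matching, the propensity score and the Cox model discard a distinction that the plan's own ascertainment can supply. This risks residual confounding if co-occurring autism relates to both C(E)TR receipt and outcome. The Cox hazard ratio for discharge, a primary-outcome estimate, is the most exposed, followed by the logistic fallback. The DiD is touched only where changes in admission risk differ by subgroup.

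The size cannot be derived from the document. The bias factors of 1.04 to 1.23 (RR 1.5 to 2) and the differences of 2 and 7 points rest wholly on assumed shares and risks. They are single-period figures within the intellectual disability category. It would be tempting to read the 2 and 7 points as the error in the DiD estimate or in the hazard ratio, but they are neither: a constant additive effect cancels in the DiD, and a risk difference does not translate directly into a hazard ratio.

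**What to change.** In the Cox model and the propensity model, replace the two-level diagnosis variable with three categories: intellectual disability only, intellectual disability with autism, and autism only. After weighting, report balance on these three categories in sub-study 1. Two-category matching can stay if the control pool is thin, since the propensity model can then carry the finer split.

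Assess how complete the level of intellectual disability is in the F7x data. Add it to the models only if it is complete enough; otherwise use it in a sensitivity analysis with a category for unspecified level.

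Cost: moving from two to three categories adds one parameter per model (2 − 1 = 1) and needs no new diagnostic extraction. There may be a small loss of precision if C(E)TR events are few. If level is added as three groups within intellectual disability (mild, moderate or more, unspecified), it costs two further parameters (3 − 1 = 2) and the work of checking the codes.
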